### Objectives

The primary objective of the study is to determine whether the incidence of PH is lower in CDH patients treated with intravenous sildenafil than in patients treated with iNO, with the primary outcome defined as the absence of PH on echocardiography on day 14 without pulmonary vasodilator therapy and without treatment failure and/or death within the first 28 days after birth. PH is defined as systolic pulmonary arterial pressure >2/3 systolic systemic pressure and/or right ventricular (RV) dilatation/septal displacement and RV dysfunction +/−left ventricular dysfunction.

The secondary outcomes are:

Change in OI after 12 and 24 hours of therapy.Overall mortality.The incidence of treatment failure which is defined as:inability to maintain preductal saturations above 85% (±7 kPa or 52 mm Hg) or postductal saturations above 70% (±5.3 kPa or 40 mm Hg).and/or increase in CO_2_ >70 mm Hg (9.3 kPa) despite optimisation of ventilator management.and/or inadequate oxygen delivery with metabolic acidosis defined as lactate ≥5 mmol/L and pH <7.15 and/or hypotension resistant to fluid therapy and adequate inotropic support resulting in a urine output <0.5 mL/kg/hour.and/or lactate ≥5 mmol/L and pH <7.15.and/or OI consistently ≥40.Time on intervention drug, defined as intervention drug free days after initiation of the intervention, calculated on day 14.Need for ECMO.Ventilator free days on day 28.The use of drugs for PH treatment during the hospital admission.The use of pulmonary and/or cardiac medication at discharge and its total duration of administration.Short-term and long-term PH on echocardiography at 24 hours, 28 days/discharge and 6 and 12 months.The incidence of chronic lung disease.The development of neurological abnormalities evaluated with ultrasound of the brain before the start of the trial, after surgery and before discharge.The external validation of the sildenafil pharmacokinetic - pharmacodynamic (PKPD) model for the pharmacokinetics and the pharmacodynamic effects of sildenafil.

Safety outcomes include adverse events due to the study drugs and the vasoactive-inotropic support (VIS) score.

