### Patients

Infants diagnosed with CDH who have PH in the first week after birth are eligible for the trial if born at or after a gestational age of 34 weeks. The diagnosis of PH is defined as at least two of the following four criteria: (1) systolic pulmonary arterial pressure >2/3 systolic systemic pressure estimated by echocardiography, (2) RV dilatation/septal displacement, RV dysfunction +/−left ventricular dysfunction, (3) pre-post ductal SpO_2_ difference >10%, (4) OI >20. Exclusion criteria are a severe chromosomal anomaly which may imply a decision to stop or not to start life-saving medical treatment, severe cardiac anomaly expected to need corrective surgery in the first 60 days of life, renal anomalies associated with oligohydramnios, severe orthopaedic and skeletal deformities, which are likely to influence thoracic, and/or lung development and severe anomalies of the central nervous system. Patients who are born in another centre and transported with iNO are also excluded from the trial. Patients who received fetal interventions (trachea balloon placement) are not excluded.

Following antenatal diagnosis, the parents are counselled and informed about the study by the clinician or research coordinator. Also, they receive a patient information letter and an informed consent form. If the patient is not born in a participating centre or the diagnosis of CDH was not known, parents are counselled after the diagnosis of CDH and are informed about the study. Also, they receive written information and an informed consent form. This informed consent form contains consent for the trial and for collection of data and material for future research.

For the development of the protocol the SPIRIT reporting guidelines have been used.^17^ This publication is based on protocol V.4, 13 June 2018.

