Postnatally, infants are treated according to a standardised protocol for patients with CDH, which is implemented in all participating centres. This protocol was developed with the available evidence and consensus between the participating centres and was updated in June 2016.^10 16^ If the patient is diagnosed with PH in the first week of life, the patient will be allocated to one of the two study drugs (figure 1). iNO is provided by a tank connected to a ventilator. Different devices are used in different centres. Some centres use integrated systems, making it impossible to disconnect the iNO tank and replace it with another gas to facilitate a blinded intervention. Therefore, the study is open label. iNO is given with a starting dose of 20 ppm, which is the maximum dose.^18 19^ Sildenafil is given intravenously, using a loading dose of 0.4 mg/kg in 3 hours, followed by continuous infusion of 1.6 mg/kg/day.^20 21^ To wean the study drugs a standard protocol is followed (figure 2). The allocated drugs will be restarted as per protocol if criteria for its use are met again before the age of 14 days. To further standardise care, an inotropic support flow chart is included in the study protocol (figure 3). After day 14 treatment of PH will be at the discretion of the local medical team and the study drug can be changed to, for instance, sildenafil orally. The use of bosentan, milrinone and prostin next to the study treatment is allowed. The use of bosentan as add on therapy is allowed and is considered as PH treatment on day 14. The intervention will be prematurely stopped when the patient meets one or more of the defined failure criteria, described in point three of the secondary outcomes. Further treatment will then be at the discretion of the medical team and will be according to the standardised protocol.^16^ iNO and sildenafil can both be given outside the study protocol. An ECMO procedure may then be started in centres where ECMO is available. Data of all patients are used in the intention-to-treat analysis.

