#### ​Data collection

Echocardiography parameters are measured by local physicians, centrally collected and reviewed by two blinded independent physicians to reduce inter-observer variation. Demographic and neonatal characteristics as well as data on the clinical course of all patients are entered in a password protected web-based database in Rotterdam (OpenClinica). On request the collected data will be available. All centres will keep a logbook of the number of non-participants, including the reasons for not participating. Study documents are securely stored at each study site for 15 years.

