### Data analysis

The patients will be analysed according to the group they are randomised to (intention-to-treat analysis). A p-value (two-sided) <0.05 is considered significant in all analyses. The primary endpoint will be analysed using multiple logistic regression with randomisation arm, centre, observed/expected head-lung ratio, position of the liver, side of the defect, defect size and ventilation modality as independent variables.^25^ If necessary, multiple imputation using the fully conditional specification method will be used to account for missing data in the independent variables. We will perform a sensitivity analyses with adjustment for the use of prostin and milrinone, to account for the effects of these vasodilators on PH.

The following analyses will be performed for the secondary outcomes. The distribution of VIS score in all study participants will be compared between t=0 and t=12 hours after initiation of drug administration using a Wilcoxon signed rank test. The distribution of changes in OI and VIS score from t=0 to t=12 and t=24 hours will be compared between the randomisation groups with a Mann-Whitney test. The overall mortality in the first year of life will be compared between the randomisation groups with Kaplan-Meier curves and the log-rank test. The number of treatment failures, the need for ECMO (in ECMO centres) and the need for medication for PH or chronic lung disease at discharge, and during the first year of life, will be compared between randomisation groups with χ^2^ tests. The number of study drug free days at day 14, the number of ventilation-free days until day 28, the fraction of days with need for medical treatment (excluding the study drug) for PH during the hospital admission and the severity of chronic lung disease using the Bancalari definition will be compared between randomisation groups using Mann-Whitney tests. Deaths will be counted as the worst outcome in these analyses, in accordance with the intention-to-treat principle. The presence of PH at 28 days/discharge, 6 and 12 months according to the echocardiographic parameters will be compared between randomisation groups with a χ^2^ test.

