### Safety reporting and trial oversight

All severe adverse events (SAEs) and suspected unexpected serious adverse reactions (SUSARs) are reported from the enrolment until 12-month follow-up. Persistent or significant disability or incapacity that was not expected with the given observed to expected lung to head ratio (O/E LHR) is evaluated as an SAE. An elective hospital admission is not a SAE. All SAEs and SUSARs are reported to the approving ethics committees in accordance with their requirements. We will report the SAEs and SUSARs that result in death or are life threatening within 7 days of first knowledge. All other SAEs and SUSARs will be reported within a period of maximum 15 days. Once a year throughout the clinical trial, we will submit a safety report to the approving ethics committees and competent authorities of the countries involved.

The trial will be monitored by qualified, independent monitors. The trial is classified as a trial with moderate risk and a specific monitoring plan is in place.

The data safety monitoring board will monitor the incidence of mortality on a continuous basis. If at some point a large difference in mortality, defined as an absolute risk increase of 25%, between the two treatment groups is noticed, the data safety monitoring board may recommend ending the study.

Insurance will cover compensation to patients who suffer harm from trial participation.

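### The adverse-event part of the safety outcome rests on open-label attribution to the study drugs, and disability counts as an SAE only if unexpected for the O/E LHR

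*Protocol article*

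**What the plan says.** After the secondary outcomes, the Objectives section states: "Safety outcomes include adverse events due to the study drugs and the vasoactive-inotropic support (VIS) score".

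Under Randomisation, intervention and blinding, the article explains that iNO equipment differs between centres and concludes: "Therefore, the study is open label". Blinded assessment is described for echocardiography only. Under Data collection, those measurements are "centrally collected and reviewed by two blinded independent physicians to reduce inter-observer variation".

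Under Safety reporting and trial oversight, all SAEs and SUSARs "are reported from the enrolment until 12-month follow-up", and that sentence sets no causality condition. The next sentence sets a condition for one class of event, which counts as an SAE when it is "Persistent or significant disability or incapacity that was not expected with the given observed to expected lung to head ratio".

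The Baseline assessment section places the observed/expected lung-head ratio among the antenatal ultrasound data. The Patients section provides for infants diagnosed later, with a consent route that begins: "If the patient is not born in a participating centre or the diagnosis of CDH was not known".

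**The concern.** Randomisation makes the total number of events comparable between arms. It does not make the number of events labelled as drug-related comparable, because the label is applied after allocation by people who know the allocation. In a critically ill newborn with CDH, an episode of hypotension or desaturation can be put down to the disease or to the drug. The Introduction gives reasons why the label might differ by arm: iNO is standard of care in the consortium's centres, and intravenous sildenafil is described as having increased the need for inotropic support. An apparent excess of harm in one arm could then come from labelling alone, or a real excess could be hidden.

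The disability rule raises a second issue. Expectedness ordinarily decides how a serious event is classified and how quickly it is reported. Here it decides whether the event is serious at all. A disability judged expected never enters the set of SAEs, so the statement that all SAEs are reported does not bring it back.

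**Working it through.** **1. Which harms depend on attribution or expectedness?** Setting Objectives, Data analysis and Safety reporting and trial oversight side by side:

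| Harm | How it is handled | Judgement needed? |
|---|---|---|
| Death in the first year | Kaplan-Meier and log-rank by arm; mortality also monitored by the data safety monitoring board | No attribution |
| Treatment failure, ECMO | χ² by arm | No attribution |
| Chronic lung disease severity | Mann-Whitney by arm | No attribution |
| VIS change to 12 and 24 hours | Mann-Whitney by arm | No attribution |
| Brain-ultrasound abnormalities | Listed secondary outcome | No attribution |
| SAEs in general | All reported, enrolment to 12 months | No causality condition on reporting |
| Adverse events as a safety outcome | Those due to the study drugs | Attribution |
| Persistent or significant disability | SAE if not expected for the O/E LHR | Expectedness |

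Only the last two rows are affected.

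**2. Do the unaffected rows cover the affected ones?** Not fully.
- Table 1 schedules the VIS score at baseline, 12 hours and 24 hours, while the allocated drug may be restarted up to the age of 14 days.
- Hypotension counts towards treatment failure only when it resists fluids and inotropes and urine output is low.
- A later haemodynamic event that is neither a treatment failure nor an SAE therefore reaches the stated safety outcome only if someone attributes it to the drug.
- The neurological secondary outcome is brain ultrasound up to discharge, and no listed outcome measures functional disability to 12 months. SAE reporting is the only stated route for that harm, and it is the route conditioned on expectedness.

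**3. Does the disability rule work for every infant admitted?** It presupposes a given O/E LHR, which is an antenatal measurement. For an infant whose CDH was not known before birth, the text does not say whether disability is then always an SAE or never one.

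**4. How attribution alone can create a difference (assumed rates).** The documents give no adverse-event rates and no attribution shares, so all rates below are assumptions. Only the arm size, 330/2 = 165, comes from the plan.

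Recorded rate = true rate × share attributed. With a true rate of 30% in both arms and 60% v 40% attributed:
- 0.30 × 0.60 = 0.18 and 0.30 × 0.40 = 0.12, mean 0.15
- standard error under no difference: √(2 × 0.15 × 0.85 / 165) = 0.0393
- standard error at these rates: √((0.18 × 0.82 + 0.12 × 0.88) / 165) = 0.0392
- chance of two-sided p<0.05: Φ((0.06 − 1.96 × 0.0393) / 0.0392) = Φ(−0.435) = 33%

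The same formula over a range:

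| True rate, both arms | Recorded, 60% v 40% attributed | Chance of p<0.05 | Recorded, 70% v 30% attributed | Chance of p<0.05 |
|---|---|---|---|---|
| 20% | 12% v 8% | 23% | 14% v 6% | 68% |
| 30% | 18% v 12% | 33% | 21% v 9% | 87% |
| 40% | 24% v 16% | 44% | 28% v 12% | 96% |

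With equal attribution the chance stays at 5%. Masking is equally possible: true rates of 30% v 20% with 40% v 60% attributed give 0.30 × 0.40 = 0.12 and 0.20 × 0.60 = 0.12, so no difference is recorded. Counting all events regardless of cause removes this source of bias.

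**The case against.** The strongest reply is that the article already protects most of the safety comparison. The Objectives sentence says that safety outcomes include these items, so the list need not be exhaustive, and the VIS score requires no causality judgement. All SAEs are reported whatever their cause. The main clinical harms are compared by arm without attribution; for instance, "The overall mortality in the first year of life will be compared between the randomisation groups with Kaplan-Meier curves and the log-rank test". Severe desaturation and refractory hypotension enter through treatment failure. All of this stands. A reader might infer that unblinded judgement decides which harms enter the comparison in general, and the documents do not support that.

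It can also be said that the article names no between-arm test of adverse events, and that definitions, adjudication and tabulation belong to the full protocol or the SAP. Their absence here is no finding. The point rests on two rules that the article does state.

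On disability, the rule sits among the reporting rules and is not written as a filter on the safety outcome. Its reference value is fixed before randomisation, which limits how far the benchmark can differ by arm, although the judgement against it remains open label. A reader might infer that expected disability vanishes from the record, or that the rule is impossible to apply after a postnatal diagnosis. The text supports neither. It says only when disability is evaluated as an SAE, and without an O/E LHR the exemption could simply lapse. What remains is that the rule is unclear for these infants.

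**Conclusion.** The point holds in a limited form. The adverse-event component of the safety outcome is restricted to events judged drug-related, in an open-label trial for which no blinded causality review is described, although SAEs are already collected regardless of cause. Separately, the disability rule lets expectedness settle whether an event is an SAE, and its application to infants without an antenatal O/E LHR is unclear.

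The effect is confined to disability and to adverse events not captured by mortality, ECMO, treatment failure, chronic lung disease or the VIS score. Its size and direction cannot be derived from the documents. The 23% to 96% range above shows a mechanism under assumed rates and would apply only if attributed counts were tested between arms. A reader might take it as a forecast of a spurious safety signal in this trial; it is not one.

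**What to change.** In Objectives, define the safety comparison as all SAEs, and any other adverse events recorded, by randomised arm regardless of attribution. Keep events attributed to the study drugs as a secondary tabulation.

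In Safety reporting and trial oversight, record every persistent or significant disability as an SAE and use expectedness only to classify SUSARs. This also settles the position of infants without an antenatal O/E LHR.

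For SAEs the first change is wording only, since they are already reported from enrolment to 12 months. For non-serious events it helps only as far as they are recorded irrespective of attribution, which the article does not say. The cost of the second change is somewhat more disability SAE reports.

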### Patients

Infants diagnosed with CDH who have PH in the first week after birth are eligible for the trial if born at or after a gestational age of 34 weeks. The diagnosis of PH is defined as at least two of the following four criteria: (1) systolic pulmonary arterial pressure >2/3 systolic systemic pressure estimated by echocardiography, (2) RV dilatation/septal displacement, RV dysfunction +/−left ventricular dysfunction, (3) pre-post ductal SpO_2_ difference >10%, (4) OI >20. Exclusion criteria are a severe chromosomal anomaly which may imply a decision to stop or not to start life-saving medical treatment, severe cardiac anomaly expected to need corrective surgery in the first 60 days of life, renal anomalies associated with oligohydramnios, severe orthopaedic and skeletal deformities, which are likely to influence thoracic, and/or lung development and severe anomalies of the central nervous system. Patients who are born in another centre and transported with iNO are also excluded from the trial. Patients who received fetal interventions (trachea balloon placement) are not excluded.

Following antenatal diagnosis, the parents are counselled and informed about the study by the clinician or research coordinator. Also, they receive a patient information letter and an informed consent form. If the patient is not born in a participating centre or the diagnosis of CDH was not known, parents are counselled after the diagnosis of CDH and are informed about the study. Also, they receive written information and an informed consent form. This informed consent form contains consent for the trial and for collection of data and material for future research.

For the development of the protocol the SPIRIT reporting guidelines have been used.^17^ This publication is based on protocol V.4, 13 June 2018.

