### Sample size calculation

The sample size calculation is based on a power analysis for the primary outcome, using previously published data on PH. Lusk *et al* showed that PH, defined as >2/3 systemic blood pressure measured on echocardiography, in CDH patients on day 14 has a positive predictive value of 0.8 for death, death or ventilation, and death or ventilator support. PH on day 14 is observed in 64% of CDH patients.^24^

Even though the definition of the primary outcome is not the same, we assume a similar outcome percentage of 64% for failing the primary outcome in our trial, the absence of PH on day 14 without pulmonary vasodilator therapy and/or absence of death within the first 28 days of life, in the iNO group. Our aim is to promote practice change; therefore, we aim for a clinically significant difference. For a 25% relative reduction to 48%, a sample size of 300 patients (150 patients per group) is needed to obtain a power of 80%. This will match a number needed to treat of 6.25. Taking missing data and the effects of correction for covariates into account, we adjust this sample size to 330 patients. In the collaborating centres 550 patients will be born in 3 years. Based on our earlier trial (CMV Versus HFO in Congenital Diaphragmatic Hernia; VICI trial) we expect to have an inclusion rate of 60%. Therefore, the inclusion of 330 patients should be reached in 3 years.

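### The primary logistic model leaves out baseline echocardiographic PH, baseline oxygenation index and age at entry, and so may forgo a modest amount of power

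*Protocol article*

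**What the plan says.** All references are to the protocol article.

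- **Entry (Patients).** "The diagnosis of PH is defined as at least two of the following four criteria". Criteria 1 and 2 are echocardiographic. Criteria 3 (pre-post ductal saturation difference above 10%) and 4 (OI above 20) are not. PH has to be present in the first week after birth.
- **Outcome (Objectives).** PH is defined by echocardiography alone and assessed on day 14. The outcome also requires no treatment failure, and an OI persistently at or above 40 is one of the failure criteria.
- **Clock (Randomisation, intervention and blinding).** The study period runs on postnatal age, not time since start: the allocated drug is restarted if its criteria recur "before the age of 14 days".
- **Baseline data (Follow up, Table 1).** Echocardiography and OI are both marked in the column before start of therapy.
- **Primary model (Data analysis).** Logistic regression on arm, centre, observed/expected head-lung ratio, "position of the liver, side of the defect, defect size and ventilation modality as independent variables". Missing independent variables are to be multiply imputed if necessary. The one sensitivity adjustment named is for prostin and milrinone.
- **Stratification.** Centre only.

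**The concern.** The model contains no measure of the infant's state at entry on the scale on which the outcome is judged. Infants may differ at entry in whether they meet an echocardiographic criterion, in OI and in age. With PH assessed at day 14 of life, entry between day 0 and day 7 leaves between 14 − 0 = 14 and 14 − 7 = 7 days from entry to assessment.

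There is reason to expect these variables to be prognostic. Baseline echocardiographic PH is the baseline value of the main outcome component, and OI also appears in the failure criteria. The Introduction says that prenatal parameters can predict lung hypoplasia but that reliable predictors of PH are lacking, so the antenatal covariates already listed need not carry the same information. Some infants are also diagnosed only after birth, so antenatal covariates may need imputing, whereas OI and echocardiography are scheduled at entry.

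In logistic regression, omitting a baseline variable that predicts the outcome given the other covariates costs power for the treatment effect. What is at stake is precision, not validity.

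**Working it through.** **Inputs from the article.** Two-sided 5% level ("A p-value (two-sided) <0.05 is considered significant in all analyses"); control failure rate 64% ("we assume a similar outcome percentage of 64% for failing the primary outcome in our trial"); sildenafil failure rate 48%; 150 per group; 80% power; total raised from 300 to 330, or 165 per group.

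**Input not in the article.** The prognostic strength of the three variables beyond the listed covariates. It is assumed below as a range.

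**Step 1: the plan's own figure.** With pooled variance under the null and no continuity correction,

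n = [z₀.₉₇₅ √(2 p̄(1−p̄)) + z₀.₈₀ √(p₁(1−p₁) + p₂(1−p₂))]² / (p₁−p₂)²

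where p̄ = (0.64 + 0.48)/2 = 0.56.

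- 2 × 0.56 × 0.44 = 0.4928, square root 0.7020
- 0.64 × 0.36 + 0.48 × 0.52 = 0.4800, square root 0.6928
- n = (1.960 × 0.7020 + 0.8416 × 0.6928)² / 0.16² = 3.838 / 0.0256 = 149.9, so 150 per group

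The stated figure reproduces. Power is 80.0% at 150 per group and 83.7% at 165. The calculation uses no baseline covariate.

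**Step 2: simulated effect of adding a baseline score.** There were 4,000 simulated trials per row, with marginal failure rates held at 64% and 48% and 150 per group. The omitted information is represented by one standard-normal score with the stated odds ratio (OR) per SD. The listed covariates have either no effect or act as a separate, independent score with OR 2.0 per SD. Monte Carlo error of each power is √(0.8 × 0.2 / 4000) ≈ 0.6 point.

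| Added score, OR per SD | No other covariate effect: omitted → included | Listed covariates OR 2.0 per SD: omitted → included |
|---|---|---|
| 1.00 | 80.1% → 79.8% | 83.4% → 83.3% |
| 1.35 | 79.4% → 80.4% | 83.1% → 83.5% |
| 1.65 | 81.0% → 82.5% | 84.4% → 86.1% |
| 2.0 | 80.4% → 83.7% | 83.0% → 86.1% |
| 2.7 | 80.1% → 86.4% | 82.0% → 88.8% |
| 3.7 | 80.0% → 89.1% | 83.7% → 91.3% |

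The gain is nil if the score adds nothing, about 1 to 3 points for OR 1.35 to 2.0, and about 6 to 9 points for OR 2.7 or more. At 165 per group, gains for OR 1.35 to 3.7 are about 0.5 to 8 points.

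**Step 3: cross-check.** If the added terms explain a further fraction R² of outcome variance, the effective size is roughly n/(1−R²). For R² = 0.10, 150/0.90 = 166.7 per group.

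| Added R² | Power at 150 per group | Total for 80% power, 300 × (1−R²) |
|---|---|---|
| 0.02 | 80.8% | 294 |
| 0.05 | 82.0% | 285 |
| 0.10 | 84.0% | 270 |
| 0.20 | 88.0% | 240 |

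**Step 4: room in the model.** At 150 per group the planned rates imply 150 × 0.64 + 150 × 0.48 = 96 + 72 = 168 failures and 132 successes. That gives reasonable room for three more terms, although the number of centre terms is not known from the article.

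**The case against.** The strongest reply is that nothing here is wrong. Entry rules are a design choice, randomisation protects the comparison, and the covariate list is prespecified, referenced and includes the stratification factor. All of that stands. Several stronger readings are tempting, and the article does not support them:

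- **Bias, or error left by chance imbalance.** Under randomisation, chance imbalance is covered by the confidence interval.
- **Power below plan.** The 80% never relied on these variables, so omitting them cannot take power below it.
- **The three variables are the strongest predictors.** No association with the outcome is reported. The listed covariates may carry part of the same information, and entry already requires two PH criteria, which narrows the range of severity.
- **Drug exposure varies from 7 to 14 days.** Only the interval to the day-14 assessment does. The drug is weaned by protocol, restarted if criteria recur and stopped on failure.
- **The measurements exist for every infant.** Table 1 shows that they are scheduled, not that they are complete.

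The echocardiographic term may also add little, since it is negative only for infants who meet criteria 3 and 4 and neither of the others. As an illustration, assume that 90% meet an echocardiographic criterion and that its OR is 3. The log-odds SD is then √(0.9 × 0.1) × ln 3 = 0.33, or OR about 1.4 per SD, close to the row with a gain of about 1 point or less.

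Finally, the full analysis plan is not shown and might extend the list. The article nevertheless states a definite set of covariates, and that set can be judged as it stands.

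**Conclusion.** The point holds as a modest efficiency gain of unknown size. The primary model omits three characteristics known, or scheduled to be known, before therapy: two bear directly on how the outcome is defined, and the third sets how long after entry it is assessed. The stated sample size is correct for its inputs. The range of 0 to about 9 points rests on assumed prognostic strengths, on a single normal score standing in for the three variables, and on that score being independent of the listed covariates. Any overlap with those covariates moves the gain towards the low end. A reader should not take the upper figure as the expected loss. The case for acting is that the change costs almost nothing.

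**What to change.** Before any outcome data are seen by arm, add to the primary logistic model:

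1. baseline OI, as a continuous variable;
2. baseline echocardiographic PH (criterion 1 or 2 met), if it varies enough to be informative, judged on data pooled over arms;
3. age at randomisation. This is preferable to age at start of study drug, which is fixed only after allocation in an open-label trial.

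Include these terms in the multiple imputation already planned for missing independent variables. Leave eligibility and timing as they are.

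The cost is an amendment to the analysis wording, three more model terms, a slightly larger imputation model and a slightly different conditional odds ratio. No new measurements are needed. Prespecification matters because, in an open-label trial, terms added later could look data-driven.
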